### Randomization

We will use permuted block randomization, stratified by HIV status, to ensure balance across study arms. The randomization sequence will be computer-generated using REDCap’s randomization module. REDCap will conceal allocation until after baseline data entry is complete, ensuring that research staff cannot foresee or manipulate assignments. The study biostatistician will generate the allocation sequence and upload it into REDCap. The research assistants will enroll participants, and REDCap will automatically assign the participant to their group after enrollment and baseline data completion. Participants will be randomized 1:1 to the intervention group (offering intervention sessions from 0 to 3 months) or the waitlist control group (offering intervention sessions from 3 to 6 months), with up to six sessions delivered over 3 months among both arms.

### Inclusion criteria

To be eligible for enrollment in the RCT, participants must meet the following criteria:Aged 15 to 24 years;Speak Nyanja, Bemba, and/or English fluently;Reside in the Matero or Chawama constituency area during the time of recruitment;Meet the following criteria based on selected items from the WHO Multi-Country Study on Women’s Health and Domestic Violence Against Women instrument:◦ GBV Exposure Criterion (Sections 7, 8, and 10): Participant reports any emotional, physical, or sexual violence, including:▪ Emotional or controlling behaviors by a current or most recent intimate partner▪ Physical violence by a current or past intimate partner since age 15▪ Sexual violence by a partner or non-partner since age 15▪ Unwanted or coerced sexual touching or sexual acts before age 15▪ Injury resulting from partner violence at any point in lifeAND/OR◦ GBV Risk/Vulnerability Criterion (Sections 6 and 11): Participant demonstrates elevated vulnerability to GBV, indicated by:▪ Endorsement of violence-supportive or controlling gender norms (e.g., obligation to obey husband, sexual obligation, justification of partner authority)▪ Restricted financial autonomy, including partner control of earnings, financial decision-making, or ability to access money/resources▪ Low confidence in the ability to secure funds independently in an emergencyExhibit moderate depressive symptoms indicated by a score of 10–14 on the 9-item Patient Health Questionnaire (PHQ-9), or common mental disorder (CMD) symptoms (e.g., depression, anxiety) as indicated by a score of 9 or higher on the 14-item Shona Symptom Questionnaire (SSQ-14); andBe living with HIV or demonstrate HIV risk behaviors, as defined by validated items from the World AIDS Foundation survey [58], including unprotected sex, multiple sexual partners, coerced sex, or transactional sex.

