**Methods:**

A hybrid implementation-effectiveness type 1 randomized controlled trial (intervention and waitlist control arms) will be conducted among 90 AGYW, aged 15 to 24, per arm with moderate depressive symptoms, lifetime GBV exposure, and HIV risk or diagnosis. The intervention comprises six individual PST sessions delivered over 3 months in church spaces. Implementation outcomes (feasibility, acceptability, fidelity), common mental disorder (CMD) symptoms (primary outcome), and exploratory outcomes (depression, anxiety, PTSD, HIV engagement, GBV attitudes, childhood adversity, coping self-efficacy) will be assessed at baseline, 3, and 6 months. The trial is powered to detect changes in CMD symptoms only. Mixed-methods data will inform feasibility, intervention refinement, and hypotheses regarding mental health as a mediator of HIV outcomes. Process evaluations will use the Consolidated Framework for Implementation Research (CFIR).

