## Methods

### Study design

We will conduct a two-arm HT1 randomized controlled trial (RCT) to evaluate the effectiveness and implementation of the adapted Friendship Bench intervention, *Mpata Yathu*, on HIV prevention and treatment, and depression outcomes among young women living with or at risk for HIV, with a lifetime history of GBV and depression symptoms in Zambia. This study will have two arms: an intervention group and a waitlist control group. This trial follows a superiority framework, testing whether the intervention improves outcomes compared with the waitlist control group. The SPIRIT figure [51] (Fig. 2; see Additional file 3 for Checklist) illustrates the timeline of enrollment, intervention, assessments, and close-out procedures for the RCT of the *Mpata Yathu* counseling intervention for AGYW exposed to GBV in Zambia. All items from the WHO Trial Registration Data Set are provided in Additional file 1. The intervention is designed to be delivered in six sessions, with one session per week. However, participants will be given up to 3 months to complete all sessions to accommodate common barriers such as caregiving responsibilities, stigma, mobility, and illness [52–55]. Counseling sessions will be scheduled to accommodate participant availability, and lay counselors will track session completion. After screening and enrollment, eligible participants will be randomized in a 1:1 ratio to either group.*Intervention group:* Participants will receive up to six individual counseling sessions between baseline and 3-month follow-up (0–3 months).*Waitlist control group:* Participants will receive usual care from 0 to 3 months, followed by the intervention (up to six counseling sessions) between 3 and 6 months.

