#### Mental health outcomes

The primary outcome is symptoms of common mental disorders (CMDs), assessed using the Shona Symptom Questionnaire (SSQ-14) [59]. The SSQ-14 consists of 14 yes/no items assessing psychological distress, with a score ≥ 9 indicating probable CMD. This outcome will be measured at 3 months and analyzed as a continuous variable, consistent with the original Friendship Bench study, which used SSQ-14 scores as a continuous measure to assess symptom reduction overtime [24]. The SSQ-14 was selected as the primary outcome measure because it is a culturally adapted and validated screening tool developed specifically for Zimbabwean and similar Southern African primary care populations. It captures symptoms of CMDs across emotional, somatic, and functional domains, and demonstrated strong psychometric properties in the original Friendship Bench trial [24].

The secondary outcome is depressive symptoms, measured using the Patient Health Questionnaire-9 (PHQ-9). PHQ-9 scores will also be analyzed using both binary and continuous analysis, consistent with the original Friendship Bench trial [24]. Although eligibility for this study includes a PHQ-9 score between 10 and 14, PHQ-9 will also be analyzed as a binary variable using a cutoff of ≥ 11 to estimate the prevalence of probable depression, as done in the original trial [24]. The PHQ-9 was selected as the secondary outcome due to its global recognition and its use in clinical settings in Zambia. Using the PHQ-9 enables broader comparability with global mental health studies and potential clinical integration. Exploratory mental health outcomes include anxiety and PTSD symptoms, assessed with the Generalized Anxiety Disorder (GAD-7) scale and Child PTSD Symptom Scale (CPSS) [61], respectively. CPPS was validated among children and adolescents in Zambia with good internal reliability (*α*> 0.80) [68].

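### The abstract and study design section describe a narrower population than the inclusion rule admits, and women can enter below the cutoff of the binary PHQ-9 outcome

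*Protocol article*

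**What the plan says.** The protocol article describes the population in several places.

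- **Abstract, Methods:** "90 AGYW, aged 15 to 24, per arm with moderate depressive symptoms, lifetime GBV exposure, and HIV risk or diagnosis". No alternative symptom route is named.
- **Study design:** women "with a lifetime history of GBV and depression symptoms in Zambia".
- **Inclusion criteria:** moderate depressive symptoms, defined as PHQ-9 10 to 14, "or common mental disorder (CMD) symptoms (e.g., depression, anxiety) as indicated by a score of 9 or higher" on the SSQ-14.
- **Exclusion criteria:** PHQ-9 above 14, or GAD-7 above 14. No PHQ-9 minimum is set for women who qualify on the SSQ-14.
- **Mental health outcomes:** the primary outcome is the SSQ-14, of which the section says "This outcome will be measured at 3 months and analyzed as a continuous variable". For the secondary outcome, "PHQ-9 scores will also be analyzed using both binary and continuous analysis". The binary form is fixed thus: "PHQ-9 will also be analyzed as a binary variable using a cutoff of ≥ 11 to estimate the prevalence of probable depression". The reason given is consistency with the earlier Friendship Bench trial, and the overlap with the entry band is acknowledged in passing: "Although eligibility for this study includes a PHQ-9 score between 10 and 14".
- **Power analysis:** only the SSQ-14 is powered. All other quantitative outcomes are exploratory and are meant to inform effect size estimates and future trial design.

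**The concern.** By the protocol's own definition, moderate depressive symptoms means PHQ-9 10 to 14. A woman admitted on the SSQ-14 with a PHQ-9 score below 10 is eligible but does not fit the abstract's description. A reader relying on the abstract would apply the results to moderately depressed women, although the rule does not require moderate depression.

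The binary PHQ-9 outcome adds a second difficulty. Its cutoff of 11 lies above some scores that qualify for entry. A woman who starts below 11 is already a non-case: she can stay one or become a case, but she cannot move from case to non-case. The outcomes section notes the overlap for the PHQ-9 route, but it mentions neither the SSQ-14 route nor how such women are handled. Depressive symptoms are the named secondary outcome, the mechanism in the Hypothesis section and one of the mediators to be tested. A shrunken binary effect could therefore mislead the planning of a later trial.

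**Working it through.** **1. The plan's own figure.** With d = 0.5, two-sided alpha 0.05 and 80% power, the normal approximation gives n = 2(1.960 + 0.842)²/0.5² = 62.8, so 63 per arm (power 0.801). Allowing for 30% attrition, 63/0.70 = 90 per arm. Both stated figures reproduce. They rest on the SSQ-14, and nothing below changes them.

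**2. Eligibility logic, with no assumptions.**
- PHQ-9 route: scores 10 to 14 are admissible, and one of these five (10) is below 11.
- SSQ-14 route: PHQ-9 scores 0 to 14 are admissible. Ten of these fifteen (0 to 9) are below the moderate band, and eleven (0 to 10) are below 11.

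These are counts of score values, not of women.

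**3. How many women: assumptions needed.** The documents give no baseline PHQ-9 or SSQ-14 distribution and no expected split by entry route. Two illustrations follow.

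(a) Let f be the share of entrants with PHQ-9 below 10, and q the share scoring exactly 10 among those at 10 to 14. The share starting below 11 is f + (1 − f)q. With q = 0.20:

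| f | share below 11 | of 180 |
|---|---|---|
| 0 | 20% | 36 |
| 0.10 | 28% | 50 |
| 0.25 | 40% | 72 |
| 0.50 | 60% | 108 |

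With q from 0.10 to 0.30 and f from 0 to 0.50, the range is 10% to 65%.

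(b) Bivariate-normal simulation, rounded and clipped to the scale limits, with the either/or rule and the PHQ-9 exclusion applied (GAD-7 exclusion not modelled). Assumed for screened women: PHQ-9 mean 8 to 9, SD 5; SSQ-14 mean 6.5 to 7.5, SD 3.5; correlation 0.5 to 0.75. With all values crossed, among eligible women:
- PHQ-9 below 10: 11 to 36% (20 to 65 of 180)
- PHQ-9 below 11: 33 to 53% (59 to 95 of 180)
- SSQ-14 below 9: 25 to 52%

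**4. Dilution of the binary contrast.** Assume that at 3 months PHQ-9 is 11 or more in 60% (control) v 35% (intervention) of women who started at 11 or more, and in 15% v 10% of those who started below. If a share s starts below 11, then pC = 0.60(1 − s) + 0.15s and pT = 0.35(1 − s) + 0.10s, so the difference is 0.25 − 0.20s. Power is for the normal-approximation test of two proportions, 63 per arm:

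| s | pC | pT | difference | power |
|---|---|---|---|---|
| 0 | 0.60 | 0.35 | 0.25 | 0.81 |
| 0.20 | 0.51 | 0.30 | 0.21 | 0.67 |
| 0.40 | 0.42 | 0.25 | 0.17 | 0.53 |
| 0.60 | 0.33 | 0.20 | 0.13 | 0.38 |

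At s = 0.40 the result depends on what happens below 11. Power is 0.63 if the intervention also prevents worsening there (15% v 5%), and 0.44 if it does nothing there (10% v 10%). All these rates are assumptions.

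**5. The primary scale.** Under the inputs of 3(b), entrants average 8.0 to 9.6 on the SSQ-14 with SD 2.1 to 3.0. An effect of d = 0.5 is then about 1 to 1.5 points (0.5 × 2.1 to 0.5 × 3.0), and at most about 4% of entrants score 2 or less. That leaves little floor effect.

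**The case against.** The strongest reply is that this is mostly editorial. An abstract condenses, the inclusion criteria are explicit and govern enrolment, Aim 1 concerns CMD symptoms rather than moderate depression, and either of two screening tools is a legitimate route into a trial whose primary outcome is the SSQ-14. The outcomes section says eligibility includes PHQ-9 10 to 14, which is not exclusive and so does not contradict the inclusion rule. It also gives its reason for the cutoff of 11: comparability with the original trial. Binary PHQ-9 is unpowered and sits beside a continuous analysis in which women below 11 can improve. Those women still inform the binary contrast, since preventing a rise to 11 counts. The article foresees mixed-effects logistic models, and further modelling detail usually belongs in a statistical analysis plan.

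Most of this stands and limits the point. It does not remove the mismatch: the abstract names the narrower route and drops the wider one. Nor does comparability with an earlier trial settle how women already below the cutoff are to be read.

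A reader might go further and infer three things that the documents do not support:
- **That many women will enter below the threshold.** No baseline distribution is given, and the share runs from 10% to 65% across the assumptions in 3(a).
- **That the primary analysis suffers because PHQ-9 entrants can have an SSQ-14 score below 9.** The SSQ-14 is analysed as a continuous score, 9 is not an endpoint, and no loss of power is shown.
- **That the randomised comparison is biased.** Eligibility is settled before allocation and applies to both arms alike, so the effect is dilution.

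**Conclusion.** The point holds in a limited form. From the text alone, the abstract and Study design describe a narrower population than the inclusion rule admits, and women on either route can start below 11 and so cannot improve on the binary PHQ-9 outcome. The size is not in the documents. Under the crossed simulation inputs, 11 to 36% of eligible women would have PHQ-9 below 10 and 33 to 53% below 11. Under the illustrative response rates, power for the binary contrast would fall from 0.81 with nobody below 11 at entry to 0.53 with 40% below. That matters for interpretation and for the planned use of these estimates in designing a later trial, not for the trial's main conclusion. This is worth correcting, at moderate priority.

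**What to change.** 1. **Population wording.** Reconcile the abstract and Study design with the inclusion and exclusion criteria, so that results are stated for the women actually eligible. As the criteria now read, that is PHQ-9 10 to 14 or SSQ-14 of 9 or more, with PHQ-9 and GAD-7 no higher than 14. Which thresholds should govern entry is for the investigators to decide.
2. **Binary PHQ-9 at 3 months.** Adjust the between-group comparison for the continuous baseline PHQ-9 score. In one illustrative simulation (63 per arm, assumed inputs), power was about 0.56 for a group-by-time contrast on the dichotomised score and about 0.72 for the adjusted comparison. Only the direction should be relied on.
3. **Supplementary result.** Report remission (below 11, the protocol's own cutoff) among women at 11 or more at baseline, beside the overall prevalence.

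The cost is wording, one covariate and one extra result, and PHQ-9 and SSQ-14 are already collected at baseline. The downsides are a broader stated population and a remission result that rests on a smaller subset of an already unpowered outcome. A table of entry route by arm would help readers but is only reporting detail.

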### Exclusion criteria

Women will be excluded if they:Require emergency treatment for any crisis (mental, physical, emotional) at the time of screeningReport severe symptoms of depression (score > 14 on PHQ-9), and/or severe anxiety symptoms using the Generalized Anxiety Disorder 7-item scale or GAD-7 (score > 14 on GAD-7)Have intellectual or cognitive disabilities that limit their ability to complete the screening tools, interact with a lay counselor and/or provide informed consent; and/orAre considered in immediate danger (e.g., reoccurring physical violence) during time of the study.Are currently receiving formal mental health counseling or psychotherapy (to avoid duplication of care and potential confounding effects).

### Study procedures for RCT participants

Recruitment, screening, and consenting will take place at both intervention and non-intervention sites across Lusaka, including churches, government health facilities, schools, and community-based organizations; the intervention will be delivered at two Catholic churches—one in Matero and the other in Chawama. These locations were identified in consultation with native Zambians who are familiar with these church settings to ensure accessibility and safety for potential participants. Private rooms within the selected locations will be used to ensure confidentiality during screening and consenting. In some cases where private rooms are unavailable, screening and consenting will take place outdoors in quiet, secluded areas to maintain privacy.

Participants will be informed whether they are eligible for the study immediately after completing the screening. Eligible individuals will be considered enrolled in the study immediately after consenting. If unavailable to screen, consent, and/or enroll during the time of recruitment, potential participants will be asked to schedule a time to complete the screening, enrolling, and/or consenting in person. The research team will conduct the screening and consenting. We will utilize the following recruitment methods:Passive recruitment: Study personnel will share a recruitment flyer with schools, churches, community-based organizations and clinical settings that serve AGYW, including youth-friendly spaces at government hospitals.Direct recruitment: Our research team will approach AGYW at selected recruitment sites (e.g., churches, schools, designated youth-friendly spaces at government hospitals during regular operating hours). Potential participants will be asked if they would like to be screened for eligibility. Interested individuals will be invited to a private or secluded space for screening by the research team, who will follow an eligibility screening script.Recruitment letters/flyers and referrals: Recruitment letters and flyers (via email, text, or hard copy) will be shared with church leaders, school staff, and members of community-based organizations that serve AGYW. They will be encouraged to share the recruitment flyer information within their networks or directly to any AGYW who they believe may be eligible, and/or refer women by directly contacting the study team.

Recruitment will occur over approximately 4 months (November 2025 to March 2026). Community outreach will occur through Neighborhood Health Committees (NHCs), defined as Ministry of Health (MoH)–recognized community health governance structures that link communities to local health facilities. Additional recruitment strategies will include direct approach at recruitment sites and referral partnerships with community organizations. To enhance recruitment and retention, flexible scheduling, reminder phone calls, church-based follow-ups, and participant-preferred contact methods will be used. Participants may complete sessions within a 3-month window to accommodate mobility, caregiving, or school responsibilities, and stigma-related barriers.

Consenting will be conducted by the local study team, including pastors, students, teachers, and youth peer navigators, who have completed training in research ethics and informed consent procedures. While some lay counselors delivering the intervention may also assist with consenting, they will not administer baseline or follow-up questionnaires to avoid potential bias in participant responses. All study personnel, including the lay counselors, will be certified in human subjects protection prior to study launch and follow safety protocols for women who may still be experiencing GBV and/or have specific mental health needs outside of the scope of our study (e.g., severe depression, suicidal ideation or attempt, psychosis).

### Study outcomes

All outcomes will be assessed at both 3-month and 6-month follow-up timepoints. The 3-month follow-up will serve as the primary endpoint for between-group comparisons (intervention vs. waitlist control). At the 6-month follow-up, only within-group changes will be assessed, as both groups will have received the intervention by this time. The waitlist control group will begin intervention delivery after completing the 3-month assessment, with no contamination expected due to the ± 1 month window applied to the time in which follow-up assessments must be completed. We outline all quantitative study outcomes with their corresponding measures and timepoints in Table 1. Table 2 outlines the HIV prevention and engagement outcomes, which are reported separately since outcome measures differ based on seropositivity status. Table 3 describes the qualitative measures, which are all implementation process measures. All instruments will be translated from English to Nyanja and Bemba using a forward–backward translation process to ensure linguistic and cultural equivalence.

**Table 1 Tab1:** Quantitative outcomes, measures, and data collection timeline (excluding HIV outcomes)

Outcome	Measure or data source	Data collection time points		
		Baseline/pre-intervention	3-month follow-up	6-month follow-up
**Mental health symptoms**				
***Common mental disorder symptoms***	Shona Symptom Questionnaire-14 (SSQ) [59]	X	X	X
***Depressive symptoms***	Patient Health Questionnaire-9 (PHQ-9) [31]	X	X	X
***Anxiety***	Generalized Anxiety Disorder (GAD-7) [60]	X	X	X
***Post-traumatic stress disorder symptoms***	Child PTSD Symptom Scale (CPSS) [61]	X	X	X
***GBV experiences and perceptions***				
***GBV experiences and attitudes***	WHO Multi-country Study on Women’s Health and Domestic Violence Against Women Instrument [1]	X	X	X
***GBV social norms and beliefs***	Perrin et al.’s Social Norms and Beliefs about Gender-Based Violence Scale [62]	X	X	X
***HIV engagement***				
***Treatment engagement (if HIV positive)***	See Table 2 for specific measures	X	X	X
***Prevention engagement (if HIV negative/status unknown)***	See Table 2 for specific measures	X	X	X
**Feasibility**				
***Recruitment time***	Time required to recruit clients and counselors (days)	X		
***Recruitment rate***	Number of eligible participants required to reach desired sample size for clients	X		
***Strictness of eligibility criteria***	Reasons for non-participation among eligible participants	X		
***Sample characteristics of clients***	Demographics of clients (e.g., age, urban/rural residence, HIV status)	X		
***Dose***	Number of sessions attended by each participant (mean number of sessions attended per arm)		X	X
***Rate of completion***	% of participants who completed all 6 sessions			X
***Time of completion***	Time required for participants to complete all aspects of the intervention (days)			X
***Referral rate***	The number of individuals referred to indicated mental health, HIV, and/or GBV services out of all individuals screened	X	X	X

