### Screening and enrollment

We anticipate screening 300 young women over 4 months to enroll 90 eligible participants. We are planning for a conservative dropout rate of 30%. This estimate draws from comparable implementation research in sub-Saharan Africa, including a trial in rural Ethiopia, which used a similar assumption to test feasibility of participant retention and study procedures [56]. This estimate allows us to account for structural barriers (e.g., mobility, stigma, early pregnancy, GBV recurrence, financial hardship, caregiving responsibilities) that commonly affect longitudinal follow-up among AGYW who have experienced GBV [53, 57]. Collecting actual retention data during the RCT will allow us to empirically estimate the true dropout rate and its variability, which will inform the design and sample size calculations of a future fully powered randomized controlled trial and for refining strategies to improve participant retention.

Participants will be considered lost to follow-up for a specific assessment (at 3 or 6 months after the baseline assessment) if they cannot be reached despite at least three documented recontact attempts using various methods (e.g., phone calls, church-based outreach, or home visits, based on participant consent and preference) during the assessment window, defined as ± 1 month from the target follow-up date. Recontact efforts will begin approximately 2 weeks prior to each window and continue throughout. No outreach will occur after the close of each window. Participants who miss the 3-month follow-up assessment may still be contacted and retained for the 6-month follow-up. Participants who voluntarily withdraw from the study will not be considered lost to follow-up.

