### Power analysis

This RCT is powered only to detect intervention effects on symptoms of CMDs, as measured by the SSQ-14, which is the primary outcome. All other quantitative outcomes—including other mental health measures, HIV engagement indicators, and psychosocial variables—will be treated as exploratory and used to inform effect size estimates and future trial design. With the proposed sample size of 126 participants (63 per arm) and using a two-sided alpha level of 0.05, the study will have 80% power to detect a medium effect size of Cohen’s *d* = 0.5 in SSQ-14 scores, which will be analyzed as a continuous outcome. This is a conservative estimate, selected to reflect a clinically meaningful but smaller effect than that observed in the original Friendship Bench trial, which reported a large effect (*d* ≈ 0.75–0.8) over a 6-month period. Accounting for 30% attrition, the sample size estimate was adjusted to account for an original sample size of 180 participants (90 per group). Since our study primarily measures outcomes at 3 months, a smaller effect size is assumed to avoid overestimating power. Between-group comparisons will be conducted at the 3-month follow-up, prior to the waitlist control group receiving the intervention. At 6 months, only within-group analyses will be conducted to assess sustained changes in the intervention group and pre-post change in the waitlist control group. No between-group comparisons will be performed at 6 months.

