## Conclusion

We discussed our protocol for a two-arm RCT of a PST intervention, *Mpata Yathu,* adapted from the Friendship Bench model, implemented in church settings to address syndemic outcomes (i.e., HIV and mental health disorder comorbidities) among AGYW with GBV histories. We anticipate that the results of our study will inform the development of larger, fully powered randomized trials of the church-based PST for GBV survivors in Zambia. Our study will also determine the feasibility and appropriateness of continuing such GBV-based interventions within church settings. Our study may also provide insight into the role in which mental health outcomes (e.g., depression, anxiety, PTSD) and psychosocial outcomes (e.g., childhood adversity and coping self-efficacy) may moderate or mediate the relationship between GBV experiences and HIV prevention and care engagement. We also hope that our trial will lead to further refinement and improvement of *Mpata Yathu* to address the unique needs and challenges faced by GBV survivors in culturally appropriate ways in Zambia and related contexts.

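### The feasibility outcome on strictness of eligibility looks only at eligible women, so it measures uptake and cannot show which criteria exclude women

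*Protocol article*

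**What the plan says.** Table 1 of the protocol article (Study outcomes, Feasibility block) has a row labelled "Strictness of eligibility criteria", collected at baseline only. Its measure is "Reasons for non-participation among eligible participants".

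Two other rows in the same block concern the path from screening to enrolment:

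- Recruitment rate: "Number of eligible participants required to reach desired sample size for clients".
- Referral rate: "The number of individuals referred to indicated mental health, HIV, and/or GBV services out of all individuals screened".

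The section on implementation outcomes gives no other definition of strictness. It points to Table 3 for the feasibility metrics, but the domains listed there are burden, responsiveness, content coverage, barriers and facilitators, and satisfaction. None concerns eligibility.

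On numbers, Screening and enrollment states "We anticipate screening 300 young women over 4 months to enroll 90 eligible participants". The Power analysis section says the sample size was "adjusted to account for an original sample size of 180 participants (90 per group"), and the Abstract also gives 90 per arm. Feasibility belongs to Aim 2, and the Conclusion expects the results to "inform the development of larger, fully powered randomized trials of the church-based PST for GBV survivors in Zambia".

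**The concern.** How strict a set of criteria is shows in the women who are screened and fail one. The stated denominator leaves out exactly those women. Under Study procedures for RCT participants, a woman learns whether she is eligible straight after screening and counts as enrolled once she consents. An eligible non-participant is thus essentially a woman who did not consent. Her reasons describe willingness or availability, because no criterion stood in her way.

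A follow-on trial would want to know which criterion costs the most recruits. The candidates include the symptom requirement (PHQ-9 or SSQ-14), the upper limits on PHQ-9 and GAD-7, HIV infection or risk, residence, and current counselling. The outcome that carries the strictness label cannot say. If reasons for declining are reported under that label, a reader may take them as evidence about the criteria.

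**Working it through.** **Inputs.** 300 women screened and 90 enrolled (Screening and enrollment); 180 enrolled, that is 126 inflated for 30% attrition (Power analysis). The documents give no consent rate among eligible women, so I take 70% to 100% as an assumption.

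**The plan's own figure.** For d = 0.5, two-sided alpha 0.05 and 80% power, n per arm = 2 × (1.960 + 0.842)² / 0.5² = 62.8, so 63 per arm and 126 in total. Inflated for 30% attrition, 126 / 0.70 = 180. The planned numbers reproduce, and nothing below depends on the power calculation beyond the target of 180.

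**Who each row covers.**

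| Table 1 row | Women covered | Shows which criterion failed? |
|---|---|---|
| Strictness | Eligible women who do not take part | No |
| Recruitment rate | Eligible women | No |
| Referral rate | All screened women | No, it counts referrals |

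**Screening flow.** With S screened, E enrolled and consent rate c among eligible women:

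- eligible = E / c
- ineligible = S − E / c
- eligible but not enrolled (the women the strictness row describes) = E / c − E
- not enrolled = S − E, which is 300 − 90 = 210 or 300 − 180 = 120

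| Enrolled | Assumed consent | Eligible | Ineligible | Covered by the row | Ineligible as share of not enrolled |
|---|---|---|---|---|---|
| 90 | 100% | 90 | 210 | 0 | 100% |
| 90 | 90% | 100 | 200 | 10 | 95% |
| 90 | 80% | 112.5 | 187.5 | 22.5 | 89% |
| 90 | 70% | 128.6 | 171.4 | 38.6 | 82% |
| 180 | 100% | 180 | 120 | 0 | 100% |
| 180 | 90% | 200 | 100 | 20 | 83% |
| 180 | 80% | 225 | 75 | 45 | 62.5% |
| 180 | 70% | 257.1 | 42.9 | 77.1 | 36% |

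In every line, the number of ineligible women covered by the strictness row is zero. That follows from its denominator and needs no assumption about consent.

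As a share of all 300 screened, the ineligible make up 57% to 70% if 90 enrol (171.4/300 to 210/300) and 14% to 40% if 180 enrol (42.9/300 to 120/300).

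**The case against.** The strongest reply is that this is one mislabelled row in a descriptive table and that little follows from it. Much of that stands.

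- **No decision hangs on the row.** The protocol sets no threshold or rule for keeping or changing criteria. A reader might infer that the next trial will be given a wrong answer. The documents do not support that: the row gives no answer on strictness, and it misleads only if its content is read as one.
- **A wrong screening target does not follow.** The number screened must be recorded for the Referral rate row, and enrolment is known, so women screened per woman enrolled can still be calculated.
- **An ineligible majority is not established.** It holds over the assumed consent range if 90 enrol, but not if 180 enrol. The protocol gives both targets.
- **The criteria are not uniformly narrow.** Several offer alternatives: GBV exposure and/or vulnerability, PHQ-9 or SSQ-14, HIV infection or risk behaviour.
- **Ineligible women are not wholly unseen.** Some of those excluded for severe symptoms may appear among the referrals, though not by criterion.
- **Refusal need not be unrelated to the criteria.** Different criteria would produce a different eligible group, whose reasons for declining might also differ. That still would not make those reasons a measure of strictness.

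It can also be said that exclusion counts by criterion are commonly left to the full protocol or the participant flow diagram. That would answer a complaint that something is missing. Here the article states a measure and a denominator, and they do not fit the label. Further detail elsewhere would not correct that definition.

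**Conclusion.** The outcome is wrongly defined. It measures uptake among eligible women, and neither it nor any other listed feasibility metric shows which criteria exclude women. That conclusion rests on the wording of Table 1 alone.

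Its size depends on the consent rate, which is assumed, and on the enrolment target, which the protocol states inconsistently. For 70% to 100% consent, 171 to 210 of 210 women not enrolled are ineligible if 90 enrol, and 43 to 120 of 120 if 180 enrol: between about 36% and 100% of those not enrolled. The range is wide, so no single figure should be quoted as the impact.

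The effect is confined to one descriptive feasibility outcome under Aim 2. Randomisation, the primary analysis, power and participant safety are untouched. Because the correction is simple, it should be made.

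**What to change.** In Table 1, redefine the strictness outcome as the number and proportion of all screened women who are ineligible, broken down by criterion failed. Where all screening items were completed, add the number failing only that criterion. A criterion with alternatives should count as failed only when every alternative is failed. Move reasons for declining among eligible women to a separate row labelled uptake.

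Reconcile the enrolment target (90 or 180 from 300 screened) as well, because the expected yield is 90/300 = 30% on one reading and 180/300 = 60% on the other, and any strictness figure will be judged against it.

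The cost is a little extra tabulation of screening records. Recruitment was planned for November 2025 to March 2026, so the change can still be made at tabulation if those records were kept. Sole-failure counts are available only where screening did not stop at the first failed criterion, so the report should state the screening order and how many women completed every item. If the change is treated as an important modification of an outcome, the Ethics approval section requires it to go to both ethics bodies.
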